#### Sub-group analyses

Because a large clinical trial on this type of intervention has never been done before, we are interested in the interventions effect on various subgroups and the effect of multiple covariates on treatment outcomes. Subgroups of particular interests and potential covariates proposed are outlined in Table 2. Treatment arms will be compared with respect to potential covariates using continuous and categorical univariate analyses.

**Table 2 T2:** List of subgroups and potential covariates

**Subgroups of interest**	**Potential covariates**
Urban vs. rural	Age
By clinic	Gender
Female vs. male	Distance from clinic
Phone ownership (owned vs. shared)	Income level
Occupational designation	Cost to attend clinic
Level of education	Level of literacy
Usual mode of transportation used	Baseline quality of life
	HIV staging
	Level of disclosure of status
	Crossover into intervention

HAART = highly active antiretroviral therapy.

#### Statistical methods

The intervention arm (SMS) will be compared against the control (SOC) for all primary analysis. We will use chi-squared test for binary outcomes, and T-test for continuous outcomes. For subgroup analyses, we will use regression methods with appropriate interaction terms (respective subgroup × treatment group). Multivariable analyses will be based on logistic regression (See Table 2) for binary outcomes and linear regression for continuous outcomes. We will examine the residual to assess model assumptions and goodness-of-fit. For timed endpoints such as mortality we will use the Kaplan-Meier survival analysis followed by multivariable Cox proportional hazards model for adjusting for baseline variables. We will calculate Relative Risk (RR) and RR Reductions (RRR) with corresponding 95% confidence intervals to compare dichotomous variables, and difference in means will be used for additional analysis of continuous variables. P-values will be reported to four decimal places with p-values less than 0.001 reported as p < 0.001. Up-to-date versions of SAS (Cary, NC) and SPSS (Chicago, IL) will be used to conduct analyses. For all tests, we will use 2-sided p-values with alpha = < 0.05 level of significance. We will use the Bonferroni method to appropriately adjust the overall level of significance for multiple primary outcomes, and secondary outcomes.

To assess the impact of potential clustering for patients cared by the same clinic, we will use generalized estimating equations [GEE] (ref) assuming an exchangeable correlation structure. Table 3 provides a summary of methods of analysis for each variable. Professional academic statisticians ([name]) blinded to study groups will conduct all analyses.

**Table 3 T3:** Variables, Measures and Methods of Analysis

**Variable/Outcome**	**Hypothesis**	**Outcome Measure**	**Methods of Analysis**
1) **Primary**	Intervention improved outcome from baseline to 6 months		
			
a) Adherence at 12 months		Percent adherence in previous 30 days >95% [binary]	Chi-squared test
			
b) Suppression of HIV viral load at 12 months		Viral load ≤400 copies/ml [binary]	Chi-squared test

2) **Secondary** Adherence percentage at 12 months	improvement occurred	Adherence % (>95%) [binary]	Chi-squared test

HIV viral load at 12 months	improvement occurred	Viral load (copies)	T-test

Immune reconstitution (change in CD4 T cell count from baseline)	improvement occurred	Cd4 T-cells/mm^3 ^(continuous)	T-test

Time to virological failure	Improvement occurred	Virological failure after successful suppression	Kaplan-Meier survival analysis

Weight gain [lbs] and BMI	improvement occurred	Change in weight (lbs) and BMI [continuous]	T-test

Occurrence of opportunistic infections (OIs)	improvement occurred	Presence of AIDS defining opportunistic infection [binary]	Chi-squared test

Time to reporting of adverse drug events (ADEs)	improvement occurred	Presence of drug-related adverse event [time to event]	Kaplan-Meier survival analysis

Deaths (all cause)	improvement occurred	All-cause mortality [binary]	Chi-squared test and Kaplan-Meier survival analysis

SF-12	improvement occurred	Quality pf life questionnaire [continuous]	T-test

Satisfaction with care provided	improvement occurred	Questionnaire [continuous]	T-test

Level of disclosure of HIV status	improvement occurred	Disclosed to a family member [binary]	Chi-squared test

Impression of stigma	improvement occurred	Questionnaire [continuous]	T-test

Family dyamics	improvement occurred	Questionnaire [continuous]	T-test

Employment attendance	improvement occurred	Questionnaire [continuous]	T-test

Household member school attendance	improvement occurred	Questionnaire [continuous]	T-test

Cell phones lost/stolen	improvement occurred	Presence of cellphone [binary]	Poisson regression

Stopped taking HAART	improvement occurred	Self-report [binary]	Chi-squared test

Required active tracing for 12 month follow-up	improvement occurred	Field officers [binary]	Chi-squared test

3) **Subgroup Analyses:**			Regression methods with appropriate interaction term
Urban vs. rural	Distance affects adherence		
Female vs. male	Sex affects adherence		
Phone ownership (owned vs. shared)	Ownership affects adherence		
Level of education	Low education affects adherence		

4) **Sensitivity Analyses:**	improvement occurred	All outcomes	
a) Per protocol analysis			a) Chi-squared/T-test test
b) Adjusting for baseline covariates			b) Multivariable regression
c) clustering among individuals within a clinic			c) GEE

IMPORTANT REMARKS:

• The GEE[11] is a technique that allows to specify the correlation structure between patients within a hospital and this approach produces unbiased estimates under the assumption that missing observations will be missing at random. An amended approach of weighted GEE will be employed if missingness is found not to be at random.[12]

• In all analyses results will be expressed as coefficient, standard errors, corresponding 95% and associated p-values.

• Goodness-of-fit will be assessed by examining the residuals for model assumptions and chi-squared test of goodness-of-fit.

Bonferroni method will be used to adjust the overall level of significance for multiple secondary outcomes.

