#### Primary outcomes

The first primary outcome is patient adherence to HAART at twelve months. (See Appendix) This is assessed by self-report using a standard questionnaire of the number of pills missed in the last 30 days and calculating percent adherence based on the expected number of doses taken. Percent adherence will be analyzed as a continuous variable and dichotomous variable. Subjects are considered either 'adherent' or 'non-adherent' using an optimal adherence cut off of > 95% of medications taken as directed.[1] Adherence is assessed at each follow-up visit and 'ever-non-adherent' will be our dichotomous outcome. The twelve month scheduled follow-up (defined, allowing for non-exact timing of clinic attendance, as follow-up up to 15 months if patients not present at 12 months) is the primary analysis. The six month assessment will allow for evaluating trends but is not the primary outcome.

The second primary outcome is suppression of plasma HIV RNA load at twelve months after initiating ART. If patients are adherent to HAART regimens, absorb the drugs normally, and if their virus is not resistant to the HAART drugs in the regimen, then plasma HIV load should be suppressed to below detectable levels (≤400 copies per ml) by six months and remain suppressed thereafter. Due to variability in when patients show up for scheduled appointments, we accept follow-up on or after 20 weeks as the six month outcome visit. Analysis of 'suppressed' (≤400 copies/ml) versus 'failure' to suppress (>400 copies/ml) at twelve months as a dichotomous variable is the primary analysis. However, decrease in plasma HIV load copies from baseline to twelve month follow-up will also be analyzed as the difference in a continuous variable from baseline to twelve months.

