### Sample size

The primary objectives of this trial to improve adherence to HAART and suppression of HIV viral load evaluated at 12 months. The sample size calculation is based on the comparison between proportions of patients with adherence rates (measured as percent of adherence >95%) in the two groups at 12 months because this is the variable that required the larger sample size. The criterion for significance (alpha) has been set at 0.05. The test is 2-tailed, which means that an effect in either direction will be interpreted.

The sample was calculated using (Cary, NC). With the proposed sample size of 247 and 247 for the two groups (ie assuming a 1:1 allocation ratio), the study will have power of 80% to yield a statistically significant result using a chi-squared test (assuming an intention-to-treat principle for the analysis) at alpha = 0.05/2 (ie using the Bonferroni correction factor for the two primary outcomes).

This computation assumes 10% improvement in 'perfect adherence' over a baseline of 75% determined from rates in a large adherence trial by AMPATH in Western Kenya which we felt is the most representative data available. [7] This difference of 10% was selected as the smallest difference that would be important to detect, in the sense that any smaller difference would not be of clinical or substantive importance. It is also assumed that this difference is reasonable, in the sense that an effect of this magnitude could be anticipated in this field of research.

Assuming attrition rates of approximately 10% we intend to over-enrol by 10% resulting in an enrolment target of at least 534 participants for randomization (267 in the Intervention, and 267 in the Control).

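### Unadjusted binary results are relative risks, but the logistic covariate-adjusted analysis is reported as coefficients, so effect sizes before and after adjustment are not on a common scale

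*Protocol article*

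**What the plan says.** All references are to the protocol article.

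- **Primary test** (Statistical methods): "We will use chi-squared test for binary outcomes, and T-test for continuous outcomes".
- **Effect measure** (Statistical methods): "We will calculate Relative Risk (RR) and RR Reductions (RRR) with corresponding 95% confidence intervals to compare dichotomous variables".
- **Adjusted model** (Statistical methods): "Multivariable analyses will be based on logistic regression (See Table 2) for binary outcomes and linear regression for continuous outcomes".
- **Place of the adjusted analysis** (Table 3, item 4): adjustment for baseline covariates is a sensitivity analysis of all outcomes, with the method given as "b) Multivariable regression".
- **Reporting scale** (remarks under Table 3): "In all analyses results will be expressed as coefficient, standard errors, corresponding 95% and associated p-values".
- **Outcome coding**: the Primary outcomes section says "Adherence is assessed at each follow-up visit and 'ever-non-adherent' will be our dichotomous outcome". Table 3 and the Appendix instead define both primary outcomes as successes (adherence above 95%, viral load suppressed).

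The article describes no step that turns a logistic coefficient into an RR, and it plans no unadjusted OR to set beside the adjusted one.

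**The concern.** Analysis 4b exists to show whether adjustment for baseline covariates changes the answer. For the size of the effect, that requires the same measure before and after adjustment. Read together, the three statements on effect measure, model and reporting scale give an RR before adjustment and a log OR after it.

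Two things then separate the numbers even if adjustment changes nothing of substance. First, an OR lies further from 1 than the RR for the same pair of proportions, and the gap is wide when the outcome is common. Second, the OR is non-collapsible: adding a prognostic covariate moves it away from 1 even when the arms are perfectly balanced on that covariate. A reader of 4b could not tell either effect from a real correction for imbalance.

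**Working it through.** **Inputs.** The article states no planned RR or OR, so there is no figure of its own to reproduce. The rates come from the Sample size section: "This computation assumes 10% improvement in 'perfect adherence' over a baseline of 75" per cent. I read this as 10 percentage points, 75% versus 85%, because the section goes on to call it a difference of 10%.

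**Step 1: the two scales at the planned rates.** RR = p2/p1 and OR = [p2/(1−p2)]/[p1/(1−p1)].

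- Success coding (Table 3, Appendix): RR = 0.85/0.75 = 1.133; OR = (0.85/0.15)/(0.75/0.25) = 5.667/3 = 1.889.
- Failure coding (complement of the planned rates): RR = 0.15/0.25 = 0.600, an RR reduction of 40%; OR = (0.15/0.85)/(0.25/0.75) = 0.529, which read as a reduction is 47%.

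The failure figures illustrate non-adherence at 12 months. The ever-non-adherent definition covers more than one visit, so its rates may be higher.

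**Step 2: sensitivity to the inputs.**

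- If the improvement were relative (75% versus 82.5%), success coding gives RR = 0.825/0.75 = 1.10 and OR = (0.825/0.175)/3 = 1.57. Failure coding gives RR = 0.175/0.25 = 0.70 and OR = 1/1.571 = 0.64.
- The Analysis plan counts missing primary outcomes as failures. Assume 10% missing in each arm: 0.9 × 0.75 = 0.675 and 0.9 × 0.85 = 0.765. Success coding gives RR 1.133 and OR = (0.765/0.235)/(0.675/0.325) = 1.57. Failure coding gives RR = 0.235/0.325 = 0.723 and OR = 1/1.567 = 0.638.

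The gap narrows but remains in every case.

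**Step 3: non-collapsibility.** Assume one balanced standard-normal covariate X with log OR b per standard deviation. Choose a so that the mean of expit(a + bX) is 0.75, then t so that the mean of expit(a + t + bX) is 0.85. The covariate-adjusted OR is exp(t). The marginal RR stays at 1.133 throughout.

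| Assumed b | Adjusted OR | Marginal RR |
|---|---|---|
| none | 1.89 | 1.133 |
| 0.5 | 1.94 | 1.133 |
| 1.0 | 2.08 | 1.133 |
| 1.5 | 2.31 | 1.133 |
| 2.0 | 2.63 | 1.133 |

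The values of b are my assumptions, as the document gives no covariate strength.

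**Step 4: can an RR be recovered from the planned model?** I simulated one data set of 200,000 participants with b = 1.0 and fitted the logistic model. The adjusted OR was 2.06. Averaging the model's predictions with everyone assigned to each arm in turn gave a standardised RR of 1.132. The unadjusted RR was 1.132, and a modified Poisson model also gave 1.132. The planned model can therefore supply an adjusted RR that is directly comparable with the unadjusted one.

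**The case against.** The strongest reply is that the article never says that ORs will be the reported adjusted measure; the term does not occur in it. The RR sentence covers dichotomous variables without limiting itself to unadjusted analyses. The remark on coefficients is plainly generic, because it also covers chi-squared tests and Kaplan-Meier curves, which have no coefficient. How a logistic result is displayed is commonly left to the analysis plan, and showing an adjusted logistic result beside an unadjusted RR is conventional.

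Much of this stands, and it keeps the point minor. It does not remove it. The article itself names the measure, the model and the reporting scale, and these do not match for the adjusted binary analyses.

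Three stronger readings are tempting, and the document does not support them.

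- **That 4b cannot be compared with the primary result at all.** Direction and significance of the logistic treatment term compare directly with the chi-squared test, and step 4 shows that the same model yields an RR.
- **That the subgroup analyses are also reported as log ORs.** The article says only that regression with interaction terms will be used and names no link function. Nor does it name one for the clustering analysis, where it says "we will use generalized estimating equations [GEE] (ref) assuming an exchangeable correlation structure".
- **That a 13% effect will be shown as 89%.** This contrast arises only under success coding, and only if someone reads an OR as an RR, which the article does not propose. Failure coding gives 40% against 47%. The Primary outcomes wording and the plan to report RR reductions both point towards failure coding, while Table 3, the Appendix and the sample size use success.

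An unadjusted OR beside the adjusted one would help, but only in part: the drift from 1.89 towards 1.94 to 2.63 in step 3 would remain.

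**Conclusion.** The point holds as a minor inconsistency. As specified, effect sizes for binary outcomes are not on a common scale before and after covariate adjustment. The size of the mismatch depends on coding: RR 1.13 against OR 1.89 for success, RR 0.60 against OR 0.53 for failure. Both rest on reading the design assumption as 75% versus 85%. The further drift of the adjusted OR through non-collapsibility is certain in direction for a prognostic covariate, but its amount rests on covariate strengths that I assumed. The primary chi-squared test and its RR are untouched, and the point does not depend on the sample size.

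**What to change.** Keep the logistic model. For the adjusted analyses of binary outcomes, add a covariate-standardised (marginal) RR and risk difference with delta-method or bootstrap 95% confidence intervals. Show them beside the unadjusted RR, with the same outcome coding in both. Amend the remark under Table 3 so that the request for coefficients does not conflict with the RR statement in Statistical methods.

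The cost is a sentence or two in the plan and one post-estimation step. Design, data collection, sample size and primary test do not change.

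Suggested wording: For binary outcomes, adjusted analyses will report the marginal relative risk and risk difference, standardised over the baseline covariates in the logistic model, with 95% confidence intervals, next to the unadjusted relative risk. Model coefficients may be tabulated in addition.

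### Single-step Bonferroni is fixed for both outcome families; it is valid, but Holm's step-down keeps the same 0.05 family-wise bound and never has less power

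*Protocol article*

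**What the plan says.** Statistical methods in the protocol article fixes the multiplicity procedure for both outcome families: "We will use the Bonferroni method to appropriately adjust the overall level of significance for multiple primary outcomes, and secondary outcomes". The remarks under Table 3 repeat it for the second family: "Bonferroni method will be used to adjust the overall level of significance for multiple secondary outcomes".

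The Sample size section shows that the single-step version is meant. The overall level is given first ("The criterion for significance (alpha) has been set at 0.05", two-sided), and the chi-squared test is then sized at "alpha = 0.05/2 (ie using the Bonferroni correction factor for the two primary outcomes").

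No step-down, gatekeeping or other sequential procedure is named. Table 3 has 18 rows under its secondary heading. The first of them, adherence above 95% as a binary variable at 12 months, repeats primary (a), so there are 17 distinct outcomes or 18 rows, depending on how one counts.

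**The concern.** Single-step Bonferroni holds every test at the strictest level, whatever the other tests show. Once one primary has been rejected at 0.025, only one hypothesis is left, and it could be tested at the full 0.05 without breaking the 0.05 family-wise bound. Bonferroni does not use that room; Holm does, with no added assumption about how the outcomes are related.

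What is at stake is power, not validity. The Objectives section expects adherence to improve and viral suppression to follow from it. Two real effects is the situation in which Holm helps most.

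**Working it through.** **Inputs from the Sample size section.** Overall two-sided alpha 0.05; 0.025 per primary; 75% versus 85% for adherence; 247 per arm; stated power 80%.

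**Inputs assumed.** The protocol gives no rates for viral suppression, no effects for the secondaries and no correlations. The adherence effect is applied to all of them. Correlations between the primaries are varied from 0 to 0.5.

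**1. The plan's own figure.** The variance sum is 0.75×0.25 + 0.85×0.15 = 0.315, so n per arm = (z for alpha + z for power)² × 0.315 / 0.10².

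- At two-sided 0.05: (1.960 + 0.842)² × 31.5 = 247.2. With pooled variance, 250.
- At two-sided 0.025: (2.241 + 0.842)² × 31.5 = 299.4. With pooled variance, 303.

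The stated 247 matches 0.05, not the stated 0.05/2. At 0.025, 247 per arm gives 70.6% power (pooled) or 71.2% (unpooled). So 71% is the right baseline for the comparison.

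**2. Two primaries, independent, both effects real.** The mean of the test statistic is 0.10 / √(0.315/247) = 2.800.

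- Power at 0.025: a = Φ(2.800 − 2.241) = 0.712.
- Power at 0.05: b = Φ(2.800 − 1.960) = 0.800.

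| | Bonferroni | Holm |
|---|---|---|
| Each primary | a = 71.2% | a + (b − a)a = 77.4% |
| Both | a² = 50.7% | b² − (b − a)² = 63.2% |
| At least one | 1 − (1 − a)² = 91.7% | the same |

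**3. The same at correlation 0.5 (simulation).** Each primary: 71% to 76%. Both: 57% to 68%. At least one: 85% under either method.

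**4. Viral suppression the stronger endpoint.** With its standardised effect set at 1.2 to 2 times that of adherence, Holm power for adherence is 78-80% against 71%. The ceiling is b = 80%, reached when viral suppression is certain to be significant.

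**5. Only one effect real (independent).** Power for the real one goes from a = 71.2% to a + (b − a) × 0.025 = 71.4%, a gain of 0.2 point.

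**6. Family-wise error.** With both nulls true and independent, it is 1 − 0.975² = 0.049 under either method. With one null true, it is 0.025 under Bonferroni and 0.025 + 0.025 × 0.712 = 0.043 under Holm. Simulation over correlations 0 to 0.8 gives 0.038 to 0.043 for Holm.

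**7. Secondaries.** The per-test level is 0.05/18 = 0.0028 (0.05/17 = 0.0029). With 18 tests, the assumed effect on each truly affected outcome, and correlation 0 or 0.3, simulated average power is:

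| Real effects | Bonferroni | Holm |
|---|---|---|
| 1 | 42% | 42% |
| 4 | 42% | 43% |
| 9 | 42-43% | 45% |
| 18 | 42% | 51-53% |

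The highest Holm family-wise error seen was 0.047.

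**The case against.** The strongest reply is that nothing here is wrong. Bonferroni is pre-specified, applied consistently and conservative, and choosing it over Holm is a matter of efficiency. That stands, and it limits the weight of the point.

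Three stronger readings are tempting, and the document does not support them.

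- A reader might infer that success requires both primaries, so that the gain in winning both is the trial's headline gain. The protocol states no such criterion. Splitting alpha between the two means that either can succeed alone, and Holm leaves the power to win at least one unchanged.
- A reader might infer that Bonferroni buys nothing. It does buy something: with one true null, its family-wise error is 0.025 rather than about 0.04, and it has simple matching simultaneous confidence intervals. Both methods stay within 0.05, however, and Statistical methods and the Table 3 remarks promise only ordinary 95% intervals. Little that the plan reports would be lost.
- A reader might infer that, because Holm also starts at 0.025, the sample-size text can stay as it is. It cannot: 247 per arm does not give 80% power at that level.

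The sizes are also open to challenge. Equal effects on the two primaries is an assumption. The Sample size section says that adherence needed the larger sample, which suggests that viral suppression has at least as much power; in that case the gain for adherence is somewhat larger. The intention-to-treat analysis counts missing outcomes as failures, so the analysed proportions will not be exactly 75% and 85%. For the secondaries, giving deaths, school attendance and lost phones the same effect as adherence is only an illustration.

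**Conclusion.** The point holds as one of efficiency, not validity. For the two primaries, with 75% versus 85% assumed on both and 247 per arm, Holm adds about 5 to 6 points of power per primary and 10 to 13 points for showing both, over correlations 0 to 0.5. It adds nothing to the chance of winning at least one, and about 0.2 point if the other effect is absent. For the secondaries the gain is about 0-2 points when few effects are real and reaches about 10 only if all are. The case therefore rests mainly on the primaries. The 71% baseline also shows a separate fault in the Sample size section that this change leaves untouched.

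**What to change.** In Statistical methods and in the remarks to Table 3, replace Bonferroni with Holm. For the primaries, compare the smaller p-value with 0.025 and, if it is significant, the other with 0.05. Within the secondary family, apply Holm in the same way, and state how many outcomes the family holds, given that its first row repeats primary (a).

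The cost is about one sentence in each place, settled before any comparison by arm. Holm has no simple matching simultaneous intervals, and its family-wise error lies closer to 0.05 while staying within it.

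Separately, restate the Sample size section. Holm's first step is still 0.025, so the text should either give the power that 247 per arm has at that level (about 71%) or give the number needed for 80% (about 300 to 303 per arm before attrition).

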### Study design

The study is a multi-site RCT. Patients will be randomized to the cell phone (SMS) intervention group versus the standard of care (SOC) control (no SMS) at a 1:1 allocation ratio (see Figure 1 Consort diagram).

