### Randomization

A project statistician generated 1:1 randomization numbers for study arm assignments using a random number generating program. The randomization was stratified in a 2:2:1 ratio to the three clinics (the rural clinic having the lower number of assignments). Written allocation of assignment is sealed in individual opaque envelopes marked with study identification numbers which are distributed to all three study clinics in sufficient quantity to allocate the target numbers of participants. After consenting to participate and meeting inclusion criteria, screened subjects are enrolled and immediately afterward are assigned to the randomized study arm by a clinician opening the sealed envelopes to determine allocation. Age, gender, and CD4 T cell counts will be assessed for balance of study arm allocation at each site.

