### Setting and participants

Subjects are recruited from three HIV comprehensive care clinics (CCC) in Kenya. One facility is an urban university-run clinic situated in a lower socioeconomic area of Nairobi, the second is an urban clinic attached to a faith-based hospital situated in a middle income area of Nairobi, and the third is a government-run clinic situated in a vast rural district of Kenya populated by pastoralists.

Patients are eligible to participate if they are initiating HAART for the first time (within two weeks before or after enrolment screening), if they are adults (at least 18 yrs old), if they owned or had sufficient access to a mobile phone (shared access is allowed if access is daily and the phone owner agrees to participate), and if they were able to sufficiently operate a cell phone to communicate using text-messaging (help by a partner is sufficient for illiterate subjects). Patients need to provide oral and written consent to participate. For patients who are illiterate, clear oral consent is obtained. Patients are excluded if they do not meet inclusion criteria or are not planning to attend the enrolment clinic for the planned study period (at least two years). Patients are considered newly initiating HAART if they have not taken HAART in at least one year and have not taken it ever for more than 2 months. Most prevention of mother to child transmission (PMTCT) regimens in Kenya include limited antiretroviral regimens and not true HAART, so participation in PMTCT is not an exclusion criteria. Therefore, the study covers a broad range of patients attending comprehensive care clinics (CCC) for ART in Kenya.

Participants are compensated for their participation time with money for lunch on study visit days (100 Kenya shillings). Patients are not provided cell phones or network airtime credit.

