#### Sensitivity Analyses

Sensitivity analysis and per-protocol analysis includes study subjects who meet certain criteria. For sensitivity, additional analysis of outcomes as stated above will include only subjects who completed follow-up at the primary 12 month endpoint. Because the SMS intervention protocol requires active participation of study subjects to respond and thus conduct the intervention as fully intended, per-protocol analyses will also be performed. Study participants in the intervention arm who respond to the weekly SMS's with an SMS back (active response) at least 80% of the time with the 48 hour time frame will be considered highly protocol-adherent; those who respond 50% to 80% of the time will be considered moderately protocol-adherent; those who respond less than 50% will be considered poorly protocol-adherent; and those that respond less than 20% will be considered least protocol-adherent. Subjects who are randomized to the SMS intervention but never respond with a return SMS, for whatever reason, will be considered as never responding and not included in the sensitivity analysis. We will also perform a sensitivity analysis to assess the impact of potential clustering of patients cared for by the same clinic.

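### The clustering sensitivity analysis applies GEE to only three clinics, where the usual robust test has a type I error of about 25-27% at nominal 5%; clinic should be handled as a stratum, and the remark on GEE and missing data needs correcting.

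*Protocol article*

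**What the plan says.** - **Number of clinics.** Under Setting and participants: "Subjects are recruited from three HIV comprehensive care clinics (CCC) in Kenya".
- **Allocation.** Patients, not clinics, are randomised, with SMS "versus the standard of care (SOC) control (no SMS) at a 1:1 allocation ratio" (Study design). Under Randomization: "The randomization was stratified in a 2:2:1 ratio to the three clinics".
- **The check.** Under Sensitivity Analyses: "We will also perform a sensitivity analysis to assess the impact of potential clustering of patients cared for by the same clinic". Under Statistical methods: "we will use generalized estimating equations [GEE] (ref) assuming an exchangeable correlation structure". Table 3 lists this as item 4c, and the row for sensitivity analyses covers all outcomes. No variance estimator, reference distribution or small-sample correction is named.
- **Use of the results.** The remarks under Table 3 ask for standard errors, intervals and p-values in every analysis. Under Statistical methods: "For all tests, we will use 2-sided p-values with alpha = < 0.05 level of significance".
- **Missing data.** The same remarks say of GEE that "this approach produces unbiased estimates under the assumption that missing observations will be missing at random", and add: "An amended approach of weighted GEE will be employed if missingness is found not to be at random".

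**The concern.** The sandwich variance in GEE is estimated from the variation between independent clusters and is reliable only when there are many. With three, it rests on about two degrees of freedom and is too small on average. A check meant to show whether the results survive clustering could then report as significant an effect that is not there, on any outcome to which it is applied.

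The design also removes most of the reason for the check. Both arms are present in every clinic, so a clinic's general level cancels from the comparison of arms and does not inflate its variance.

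The missing-data remark is a separate, smaller matter. It sets the conditions for ordinary and weighted GEE one step too far, so an analyst who followed it would rely on weighting in a case that weighting does not cover.

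**Working it through.** The documents give no error rate for the GEE analysis, so there is no stated figure to reproduce.

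**Inputs.** Three clinics (Setting and participants) in ratio 2:2:1 (Randomization); 1:1 allocation (Study design); target 534 (Sample size), so 534 × 2/5 ≈ 214 and 213, and 534 × 1/5 ≈ 107; control adherence 75% (Sample size); two-sided 5% (Statistical methods). Assumptions: no true effect; clinic adherence rates either all 75%, or 75/80/65%, or 80/75/60%.

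**Step 1: size of the bias.** Let d_k be the difference between arms in clinic k, w_k = n_k/N, and D = Σ w_k d_k. Write Var(D) = c, so Var(d_k) = c/w_k. The sandwich variance is in essence V = Σ w_k²(d_k − D)². Its mean is

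E(V) = Σ w_k²(c/w_k − c) = c(1 − Σ w_k²) = c(1 − 0.16 − 0.16 − 0.04) = 0.64c.

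The variance is understated by 36% on average, and it also varies widely from trial to trial.

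**Step 2: type I error in closed form.** For three equal clinics, E(V) = (2/3)c and the Wald statistic is √(3/2) times a t variable on 2 df. For that distribution, P(|t| > x) = 1 − x/√(2 + x²).

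- Sandwich, z test: x = 1.96 × √(2/3) = 1.600, giving 1 − 1.600/√4.561 = 25.1%.
- Sandwich, t on 2 df (critical value 4.303): x = 4.303 × √(2/3) = 3.513, giving 1 − 3.513/√14.34 = 7.2%.
- Bias-reduced sandwich (each deviation divided by 1 − w_k = 2/3, so V becomes 9/4 as large), z test: x = 1.96 × √(3/2) = 2.400, giving 1 − 2.400/√7.762 = 13.8%.

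**Step 3: simulation at 2:2:1.** Logistic GEE, exchangeable, clinics of 214/213/107, allocation balanced within clinic or simple, 3,000 null trials in each of six scenarios:

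| Analysis | Type I error at nominal 5% |
|---|---|
| GEE, sandwich SE, z test | 25.7% to 27.1% |
| GEE, bias-reduced sandwich, z test | 12.8% to 14.9% |
| GEE, sandwich SE, t on 2 df | 7.4% to 8.2% |
| GEE, model-based SE | 4.2% to 6.8% |
| Clinic-stratified risk difference (40,000-trial runs below) | 5.0% to 5.2% |
| Primary chi-squared test, allocation balanced per clinic | 4.1% to 4.9% |

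Some GEE fits stopped at their iteration limit. A check that needs no iteration (risk difference with its sandwich variance, independence working correlation, 40,000 trials per setting) gave 25.2% to 26.1% for the sandwich z test. The closed form agrees with both. A separate run of 1,500 trials gave a mean reported SE of 0.138 against a true standard deviation of 0.199, a ratio of 0.69, and about 22% rejection at nominal 2.5%. Clinic rates and the form of allocation hardly matter: the cause is the number of clinics.

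**Step 4: the missing-data remark.**

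| Method | Condition in the remark | Condition in general |
|---|---|---|
| Unweighted GEE | Missing at random | Missing completely at random, or missingness depending only on covariates in the model |
| Weighted GEE | Not at random | Missing at random, given a correct model for missingness |

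Neither handles data missing not at random. The observed data cannot establish that state, so it cannot be a finding that triggers a method.

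**The case against.** **Variance estimator.** The article does not name one, and such detail may sit in a fuller plan. This stands: the 25-27% is conditional on the usual sandwich z test, and model-based errors would be near nominal. It does not clear the choice of method. The two corrections tried still exceed 5%, and model-based errors give up the protection against a wrong correlation structure.

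**Status.** A reader might infer that the trial's own error rate is about 27%. The documents do not support that. Item 4c is a sensitivity analysis, and neither the primary chi-squared tests nor the sample size uses GEE. A reader might also infer that GEE will be offered as the more conservative check. The article says only that it will assess the impact of clustering.

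**Interaction already planned.** Table 2 lists clinic as a subgroup, and Statistical methods plans subgroup-by-treatment terms. This stands: the treatment-by-clinic interaction is not missing. What is lacking is a sound clinic-adjusted main effect.

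**Missing data.** A reader might infer that the primary results are exposed. They are not: under Analysis of primary and secondary outcomes, missing primary outcomes count as failures, and multiple imputation is planned for data not directly related to adherence. For one 12-month outcome per patient, ordinary GEE is also valid if missingness depends only on modelled covariates. If the authors meant completely at random where they wrote at random, the remark would be nearly right. As worded, it is not.

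**Conclusion.** The concern holds as a point of secondary weight. GEE on three clinics is a poor tool for a design that randomises within clinic. The type I error at nominal 5% is about 25-27% with the usual sandwich z test, about 7-15% with two common corrections, and near nominal only with model-based errors. A clinic-stratified analysis holds 5%. These figures assume no true effect, clinic sizes close to 2:2:1 and the clinic rates stated above; they barely change across those rates. The effect is confined to the sensitivity analyses, where it touches all outcomes.

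The missing-data remark is wrong as written. No size is attached to that error, and it matters mainly for secondary and completers-only analyses.

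**What to change.** 1. In Statistical methods, Sensitivity Analyses and Table 3 item 4c, replace GEE with an analysis that treats clinic as a stratum or fixed effect: Mantel-Haenszel for binary outcomes, or logistic or linear regression with two clinic indicators and model-based standard errors. For time-to-event outcomes, stratify by clinic. Refer to the planned subgroup analysis for the treatment-by-clinic interaction.
2. Rewrite the remark under Table 3. Unweighted GEE is in general valid when data are missing completely at random, or when missingness depends only on modelled covariates. Weighted GEE extends this to missing at random. Data missing not at random call for a delta-adjusted or tipping-point analysis, planned in advance and not triggered by a finding. If GEE is dropped altogether, restate the remark for the methods that remain.

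The cost is a few lines of wording and simpler code. Design, data collection, sample size and primary analysis stay as they are.
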